### 3.1. Primary outcome measure

#### 3.1.1. Positive and negative schizophrenia symptom scale (PANSS) negative symptoms subscale

The healthcare professional evaluates the patients with PANSS Negative Symptoms subscale (Cronbach’s alpha of 0.83, Kay et al., 1988; von Knorring and Lindström, 1992) at baseline, at week 6 at and after week 12, PANSS Negative Symptoms subscale will also be collected in the follow-up session; 6 and 12 months after finishing the intervention.

### 3.2. Secondary outcome measures

#### 3.2.1. Positive and negative schizophrenia symptom scale (PANSS), clinical global impression severity (CGI-S), and improvement (CGI-I)

The healthcare professional evaluates the patients with general PANSS and Positive Symptoms subscale (Cronbach’s alpha of 0.73 on the positive subscale and 0.87 for general psychopathology, von Knorring and Lindström, 1992) at baseline, at week 6 at and after week 12, Clinical Global Impression Severity (CGI-S) before session 1, at week 6 and after week 12 and Clinical Global Impression Improvement (CGI-I) at session 12 on week 6 and after week 12 are done by psychiatrist, family member or other next of kin and the patient on the same timeline. General PANSS and Positive Symptoms subscale, CGI-S and CGI-I will also be collected in the follow-up session; 6 and 12 months after finishing the intervention.

#### 3.2.2. Quality of life, social performance, and depressive symptoms

Patients will fill in quality-of-life questionnaires (EQ-5D-5L) before, after the intervention and at follow ups. The patients’ psychiatrist and a person who knows the patients, such as a family member, will evaluate the state of the patient before and after the intervention, and then, the family member will also be asked about their experience on burden of care. The Personal Social Performance scale (PSP, internal consistency reliability for the four items exceeding 0.70 for people with schizophrenia, Kawata and Revicki, 2008) assesses socially useful activities, personal and social relationships, self-care and disturbing and aggressive behaviors. The Calgary Depression Scale for Schizophrenia (CDSS, high inter-rater reliability with an intraclass correlation of 0.895 and Cronbach’s alpha 0.79 for people with schizophrenia, Addington et al., 1993) is a nine-item clinician rated outcome measure that assesses the level of depression in people with schizophrenia.

#### 3.2.3. Brain imaging

To investigate whether the InMotion intervention will enhance cognitive processes and their underlying neural functions, behavioral tests with brain imaging on attention and emotion regulation will be conducted (Balconi et al., 2015; Popov et al., 2019). Cortical activity will be measured with a combined EEG-fNIRS system (fNIRS: Sport 2, Nirx Medical Technologies, Los Angeles, CA, USA; EEG: G.tec medical engineering GmbH, Schiedlberg, Austria). The cap will have 16 fNIRS sources and 16 detectors over the frontal, and parietal brain regions to measure cognitive and motor activity, respectively. The cap will also have 64 EEG electrodes distributed throughout the head (10–20 system; Jasper, 1958). Eye tracking glasses have small cameras to detect the movements of the pupils, amount of saccades and dilation of the pupil. Eye-tracking (Levy and Gooding, 2010; Morita et al., 2017, 2019; Wolf et al., 2021) and EEG-fNIRS will be used to evaluate cognitive functioning.

Patients will conduct the following tasks during brain imaging and eye tracking: (a) cognitive tests with region of interest (ROI) on the prefrontal cortex: Stroop task (cognitive interference; Stroop, 1935; MacLeod, 1991), expectancy AX Continuous Performance Test (AXCPT; context processing; Ochsner et al., 2002; Barch et al., 2003; Braver, 2012), verbal fluency (cognitive paradigms related to prediction error as described above), and (b) emotion regulation with ROI on the frontal cortex: induction and regulation with specific positive (happiness) and negative (disgust) emotions.

#### 3.2.4. Motion capture

Movement of the participants will be recorded with the Qualisys Motion Capture system consisting of 12 cameras (Arqus A12, Qualisys AB, Gothenburg, Sweden) during the movement intervention on sessions 2 on week 1, 12 on week 6 and 23 on week 12. Each participant and the facilitators will have reflective markers attached to the skin on their hands, knees and elbows (six sensors in total per person) which they will wear throughout the movement session. The markers are small and light and will not influence movement.

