**Methods:**

The study is a mixed-method randomized controlled trial to evaluate the effects of a 12-week intervention for adults with schizophrenia. The treatment group (30 participants) will receive the intervention in addition to standard care and the control group (30 participants) only standard care. The intervention consists of 24 biweekly sessions with a duration of 60 min. The pre-test (weeks from 4 to 2 prior to the intervention) and post-test (week 12) include clinical measure (PANSS), quality of life, social performance, movement quantity, brain function and eye tracking measures. In addition, a treatment subgroup of 12–15 participants and their family member or other next of kin will complete a qualitative interview as a part of their post-test. Two follow-up tests, including clinical, quality of life, brain function and eye tracking will be made at 6 and 12 months from the completion of the intervention to both study groups. The primary outcome is change in negative symptoms. Secondary outcome measures include general and positive symptoms, quality of life, social performance, movement quantity, brain function and eye tracking. Explorative outcome includes patient and family member or other next of kin interview.

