The secondary aim is to evaluate potential change in (a) general and positive symptoms of schizophrenia, (b) quality of life, depression and social performance (c) levels of physical activity, physical function and general health indicators, and cortical aspects of (d) error detection and conflict resolution on the prefrontal cortex, (e) emotional induction and regulation on specific emotions on the frontal cortex, (f) full-body movement quantity and rigidity, (g) cognitive function such as memory and fluency of speak, and (h) to explore the participants experiences of taking part in the intervention and any experienced change from it. Similarly, experiences from their related parties (a family member or other next of kin, nursing staff) will be collected regarding the influence of the intervention in the participants (Bryl et al., 2020). Our hypothesis is that, in comparison to the control group, the intervention group will show (i) strengthened physical health, function and reduced sedentary behavior, (ii) improvement in cognitive control and emotion regulation (Davis, 1981; Martin et al., 2016) and changes in their neural correlates (Balconi et al., 2015; Popov et al., 2019), and (iii) increased mobility and reduced rigidity in movement in the schizophrenia patients over the intervention (Bryl and Biondo, 2021) which can be also seen as increased fluidity and quantity of movement measured with Motion Capture (Poikonen et al., 2018).

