### 2.5. Modes of delivery

The intervention covers various themes through three different parts (4 weeks per part) with the aim to improve clinical symptoms, physical fitness, cognitive skills and emotion regulations. The intervention was developed by a team consisting of a neuroscientist, a psychiatrist, dance teachers and physiotherapists with previous experience in designing dance and movement interventions for different target groups with internalizing problems (Duberg et al., 2013), functional abdominal pain (Högström et al., 2022) and profound intellectual and multiple disabilities (Lundqvist et al., 2022). The intervention is further described in Table 1. The exercise is partly accompanied by instrumental music and recorded nature sounds and partly made in silence paying attention to one’s own bodily rhythm. The exercise consists of tasks related to cardio and strength training, balance, conscious breathing, body awareness, mental imagery (nature visualizations), flexibility, emotional expression, and movement anticipation together with the facilitator and fellow participants. All the tasks are practiced during a flow of 60-min exercise without any major breaks. To meet the needs of the participants in the group, adjustments and modifications will be presented when necessary. Complexity and physical intensity of the tasks will gradually increase over the 12 weeks intervention periods.

**TABLE 1 T1:** Content of the biweekly 12-week intervention on mixed exercise program with creative movement for adults with schizophrenia.

Minutes	Section	Description	Purpose
		Gathering in a circle	Establishing a feeling of being included
2–4	Body scan	Scanning through the body parts Part 1 (moving), Part 2 (self-massaging and tapping), and Part 3 (moving)	Body awareness Hedlund and Gyllensten, 2010; Ferri et al., 2012; Martin et al., 2016; Gökcen et al., 2020
3–7	Gentle movement, flexibility (warm up/preparation)	Stretching arms, sides, neck, rotating shoulders, back, hip, and knees	Body awareness, increased blood-circulation and synovial fluid, stimulate mental presence. Hedlund and Gyllensten, 2010; Ferri et al., 2012; Martin et al., 2016; Bryl et al., 2020
8–10	Cardio	Reaching, jumping, walking, running	Strengthen cardio-vascular function. Soundy et al., 2014; Firth et al., 2015; Vancampfort et al., 2015b; Cheng et al., 2017
8–10	Choreography	Memorizing a dance sequence	Enjoyment, coordination, body awareness Firth et al., 2017a,b; Chen et al., 2018

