At session 2, 12, and 23 motion capture will be recorded. Those sessions will take place at the movement laboratory. Participants and one instructor will wear small reflex balls on six points: hands, elbows and knees, while doing the training session. Setting up will be done by an engineer at the movement laboratory or the doctoral student. On week 6 of the intervention the same procedure of tests, apart from the accelerometer, cognitive tests and functional brain imaging, will be repeated. After the last session, about two participants and their family members or other next of kin from each group will be purposefully selected for interview. The get a heterogenic group, we will strive for a variation regarding age, gender, participation rate and severity of disease. The participants and their family member or other next of kin will receive written and oral information about the qualitative study (including assurance of voluntariness and confidentiality), before signing a written consent. After finishing the intervention at week 12 all tests from baseline will be repeated in 1–2 weeks. This will also be done after 6 and 12 months, excluding the accelerometer.

The pilot study was conducted in the same way, except there was no control group or randomization procedure nor cognitive or brain imaging measures, nor will there be any follow-up tests in 6 or 12 months.

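### The motion-capture hypothesis is framed against the control group, but motion capture is recorded only inside intervention sessions, so that comparison cannot be made

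*Protocol article*

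**What the plan says.** **The hypothesis.** Section 1.5 opens its list of secondary hypotheses with "Our hypothesis is that, in comparison to the control group, the intervention group will show" and then gives three items. Item (iii) is "increased mobility and reduced rigidity in movement in the schizophrenia patients over the intervention", which is also expected to appear as "increased fluidity and quantity of movement measured with Motion Capture".

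**The recordings.** Section 2.11 states "At session 2, 12, and 23 motion capture will be recorded" and describes who is recorded: "Participants and one instructor will wear small reflex balls on six points: hands, elbows and knees, while doing the training session". Section 3.2.4 places the recordings "during the movement intervention on sessions 2 on week 1, 12 on week 6 and 23 on week 12". In Table 2 the motion-capture row is marked only in the three session columns. It is blank at baseline, the week 5–7 visit, the week 12 test visit, and months 6 and 12.

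**The control arm.** Under section 2.2 the 30 controls have standard care, and links to the session videos reach them only once the 12-month follow-up is over.

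**The variables.** Section 3.3.2 derives two quantities from motion capture: movement quantity, taken to reflect mobility, and a smooth-to-jerky quality score, taken to reflect rigidity.

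**The programme.** Section 2.5 divides the 12 weeks into three parts of four weeks and adds: "Complexity and physical intensity of the tasks will gradually increase over the 12 weeks intervention periods".

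**The abstract.** It says that the pre-test, 4 to 2 weeks before the intervention, and the "post-test (week 12) include clinical measure (PANSS), quality of life, social performance, movement quantity, brain function and eye tracking measures".

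**The concern.** A randomised comparison needs the outcome measured in both arms. Here a hypothesis worded as intervention against control rests on an instrument used only in sessions that controls never attend. No analysis plan can repair this later, because the control data will not exist.

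The fallback is the change within the intervention arm, but the recorded sessions are not the same exercise repeated. They sit at different points of a programme that is meant to become harder, and the first comes after training has begun. If the hypothesis stays as worded, the trial must either drop it at reporting or present an uncontrolled change under a heading that promises a controlled one.

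**Working it through.** The plan gives no figure to reproduce here. The check sets the measurement schedule against the hypothesis.

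**1. When the recordings fall.** The programme has 12 weeks × 2 sessions = 24 sessions. For session *s*, week = *s*/2 rounded up, sessions already completed = *s* − 1, and programme part = week/4 rounded up.

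| Session | Week | Sessions already completed | Part |
|---|---|---|---|
| 2 | 1 | 1 | 1 |
| 12 | 6 | 11 | 2 |
| 23 | 12 | 22 | 3 |

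The weeks agree with section 3.2.4. Table 2 heads the first column week 2. Either way, session 2 comes after the start and falls in part 1.

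**2. Who is recorded.** Intervention arm: up to 30 participants on 3 occasions. Control arm: 0 of 30, because markers are worn during training sessions and controls have none. The general statement in section 2.2 that both groups are measured at follow-ups does not supply the data, since Table 2 has no motion capture at any follow-up.

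**3. Recordings before exposure.** None in either arm: Table 2 has no entry at baseline.

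**4. What can be estimated.** The hypothesis needs (change in intervention arm) − (change in control arm). The second term is missing for both motion-capture variables. What is left is session 23 minus session 2 in one arm, which combines:

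- any true change in how participants move;
- practice and the passage of time;
- the planned increase in complexity and intensity (section 2.5), across three parts that section 2.15 describes as having separate themes.

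The article names no fixed task performed identically at all three recordings.

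**5. Is there a substitute?** For everyday activity, yes. Table 2 has the accelerometer at baseline and week 12, and section 3.2.6 says it records sedentary and active time and intensity, so the arms can be compared. For rigidity or fluidity, no: no other listed instrument is assigned to it.

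**The case against.** **Item (iii) can be read as within-arm.** It speaks of change in patients over the intervention, aim (f) speaks of potential change, section 3.3.2 speaks of changes, and no between-group motion-capture test is written out. This supports the view that the fault may be a loosely worded opening clause. It does not remove the fault: that clause governs all three items, and both arms consist of patients.

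**Stronger readings that the documents do not support.**

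- A reader might infer that the choreography differs at each recording. Sections 2.5 and 2.15 give separate parts and themes with rising difficulty, but Table 1 lists one structure and describes only the body scan as varying by part. Different choreography is plausible, not stated.
- A reader might infer that the protocol takes more movement as less rigidity. It does not: section 3.3.2 uses separate measures. Nor do the documents show in which direction harder tasks would push the smoothness score, so for rigidity the point is that change cannot be attributed, not that it is biased a known way.
- A reader might infer that the abstract promises motion capture at baseline. It says movement quantity without naming the instrument. Section 3.3.2 uses that term for motion capture, but the accelerometer is also possible. The wording is ambiguous.
- A reader might infer that movement has no controlled measure at all. The accelerometer provides one for everyday activity.

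**Other points that stand in part.** An instructor also wears markers, which could serve as a reference for the movement demanded, though no such use is stated and an instructor does not replace untreated patients. Only one of 24 sessions precedes the first recording, so the lack of a true baseline is a smaller weakness than the lack of controls. The Discussion already asks for caution with secondary outcomes, but caution cannot supply missing control data.

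**Conclusion.** The between-group part of hypothesis (iii) cannot be tested with motion capture as scheduled: 0 of 30 controls recorded and 0 recordings before the intervention, for both movement quantity and smooth-jerk quality. Rigidity is left without any controlled measure; everyday activity is not. The within-arm change from session 2 to session 23 is uncontrolled and confounded with planned progression of the tasks.

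This is a should-fix. Motion capture is a secondary outcome, and the primary outcome, its analysis and the randomisation are untouched. The conclusion assumes that Figure 1, which could not be seen, adds no control recordings; sections 2.11 and 3.2.4 and Table 2 agree that there are none.

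**What to change.** 1. In section 1.5, take the motion-capture outcomes out of the sentence that compares with controls. Suggested wording: *In the intervention group only, we will describe the change in movement quantity and smoothness from session 2 to sessions 12 and 23; this is exploratory and is not a test of the intervention against control.*
2. In Table 2 and section 3.2.4, label motion capture as single-arm, exploratory and descriptive.
3. In section 3.3.2, restrict the comparison to task segments common to the three recorded sessions.
4. In the abstract, state whether movement quantity at pre-test means the accelerometer, and make it agree with Table 2.

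The cost is text edits, the selection of common segments, and the loss of one between-group claim.

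Optional, only if the sponsor wants to keep that claim: record a short fixed movement sequence in both arms at the baseline and week 12 visits. Baseline is already in the movement laboratory (section 2.11), but the location of the week 12 tests is not restated there. Each visit already takes about 150 minutes, and markers must be set up by an engineer or the doctoral student. This is an added procedure with a real burden, which the documents do not allow to be costed.

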#### 3.2.5. Body awareness

Patients will also fill in Body Awareness Questionnaire (BAQ; Shields et al., 1989) before, after the intervention and at follow ups.

#### 3.2.6. Physical measures

Physical function and status will be measured at baseline, half-time through the intervention, after the intervention and at follow up 6 and 12 months. The measures are the following: (1) Postural stability test (Van der Heijden et al., 2019) with participant standing on a force plate, (2) chair stand test (Jones et al., 1999) to measure leg strength, (3) weight, length, BMI and waistline, (4) blood pressure measured by blood pressure monitor, (5) resting heart rate, (6) breathing frequency, and (7) everyday activity which is measured by an accelerometer which the participants will wear around their waist for 7 days in a row to collect the amount of time spent sedentary vs. active, and the intensity of the activity.

#### 3.2.7. Qualitative interviews

To capture the participants’ experiences of taking part of the intervention, individual semi structured interviews on the topic will be conducted with 15–20 participants in the intervention groups (Bryl et al., 2020). The sample size has been set with the intention to catch a width of different experiences. The interviews will be conducted immediately after the last session, to have the experience as fresh as possible. The participants self-selected expressions, own reflections and insights will add to the quantitative measures and contribute to a wider understanding of the phenomenon. The questions concern how the participants experienced being part of the InMotion intervention, whether and how the intervention influenced their health and everyday life, as well as reflections on different perspectives such as the group format. Moreover, the family member or other next of kin of these participants will also be asked to participate in an interview. The interviews will be face to face, conducted by the research team, and get to share their experience of the intervention as well as eventual effects from it.

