### 2.7. Sample size

The sample size is calculated according to the primary outcome PANSS. For the primary outcome (improved negative symptoms according to PANSS after 12 weeks), the total number of required study participants was calculated (Curcic et al., 2017). Calculation was based on a minimum improvement of 15% on total PANSS score between the intervention and control group. With a power of 80% and a significance level of 0.05, we calculated the sample size to be *N* = 60 (30 intervention + 30 control participants), including a 25% dropout rate.

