In the pilot study, we tested the feasibility of biweekly attendance, which might be challenging for the participants with schizophrenia. However, in the pilot study, there was a high attendance rate and no dropouts. Nonetheless, we are aware that biweekly commitment implies a behavioral change that can be hard to achieve for this target group. Thus, it is interesting to investigate if the format of this intervention can influence motivation, retention, and interest to participate regularly.

The results from this study will broaden the knowledge of the ways non-pharmacological interventions can be valuable for reducing the burden of schizophrenia for patients themselves, their families, and the healthcare system. Mixed physical exercise with creative movement could be an example of an easy-access joyful intervention as a complementary treatment.

To conclude, this randomized controlled study with 60 participants will investigate the effects of combined physical, creative and social training in adults with schizophrenia. The primary aim is to study the effects of the intervention on negative symptoms of schizophrenia, but several other aspects, such as physical skills and health-status, cognitive and emotional capacity and brain functions related to them as well as movement quantity and mimicry, will also be studied. The results from this intervention study may provide useful information and potentially a complementary treatment to use for caregivers in primary healthcare and psychiatric in- and outpatient clinics.

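### Interviewee selection and interviews are both tied to the end of the last session, with no stated route to intervention participants who stop earlier, so the accounts of experience will come mainly from those still attending

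*Protocol article*

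**What the plan says.** Section 2.11 sets the selection: "After the last session, about two participants and their family members or other next of kin from each group will be purposefully selected for interview". It adds that "we will strive for a variation regarding age, gender, participation rate and severity of disease".

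Section 3.2.7 sets the timing: "The interviews will be conducted immediately after the last session, to have the experience as fresh as possible". It gives the number ("individual semi structured interviews on the topic will be conducted with 15–20 participants in the intervention groups"), explains that this number was chosen to capture a breadth of experiences, and describes the content: "The questions concern how the participants experienced being part of the InMotion intervention, whether and how the intervention influenced their health and everyday life", together with reflections on matters such as the group format. Next of kin are recruited through the interviewed participants.

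The Methods part of the abstract gives a different number ("a treatment subgroup of 12–15 participants and their family member or other next of kin will complete a qualitative interview") and makes the interview part of the post-test. Table 2 likewise lists it under the week-12 assessments, as an exploratory outcome.

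Three other places bear on the point. Section 2.7 sizes the trial at 30 per arm, "including a 25% dropout rate". Section 2.15 has the instructors note adherence and has notes made on participants who discontinue or deviate. Section 7, after acknowledging that attending twice a week may be hard for this population, says "it is interesting to investigate if the format of this intervention can influence motivation, retention, and interest to participate regularly".

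**The concern.** The selection rule and the interview timing both point to the same moment, the end of session 24. Someone who left in week 3 is unlikely to be present then, and the reason given for the timing, a fresh experience, cannot be met for that person. No step is described for inviting people as they leave. Because relatives are reached through the selected participants, the relatives of early stoppers are likely to be missed as well.

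This works against two aims of the same sections: a breadth of experiences, and variation in participation rate. A low attender who still comes at the end satisfies the second aim in part. A person who stopped is the far end of that range and probably holds the least favourable view of the format. If such people are largely absent, the reported experience leans towards those whom the programme suited.

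The main trial is also the first realistic chance to hear these accounts. The pilot had two participants and no dropouts, and section 6 says that it does not evaluate attendance or dropout.

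**Working it through.** **Inputs**
- Intervention arm: 30 (section 2.7).
- Dropout allowance: 25% (section 2.7).
- Interviews: 12-15 (abstract, Methods) or 15-20 (section 3.2.7); about two per group (section 2.11), with groups of 4-6 (section 2.2).

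**Check of the plan's own dropout step.** The total of 60 cannot be rebuilt, because the article gives no standard deviation or baseline mean for the 15% PANSS difference. The inflation step can be checked: 22 / (1 - 0.25) = 29.3, rounded up to 30. So 30 per arm is consistent with about 22 evaluable per arm.

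**Expected early stoppers.** 30 × 0.25 = 7.5, that is 7-8 people, leaving 30 - 7.5 = 22.5 still attending. This assumes that the allowance applies equally to both arms and that study dropout means stopping the sessions. The article states neither.

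**Early stoppers in a proportional sample (interviews × 0.25)**
- 12 interviews: 3.0
- 15 interviews: 3.75
- 20 interviews: 5.0

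This gives about 3-4 among 12-15 interviewees and about 4-5 among 15-20. If only people still attending are reached, the number is zero. Purposive selection need not be proportional, so these figures show scale and are not a target that the plan has missed.

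**Room for purposive choice among those still attending.** 12 / 22.5 = 53%, 15 / 22.5 = 67% and 20 / 22.5 = 89%. At the counts in section 3.2.7, two-thirds to nine-tenths of those still attending would be interviewed. Most of the remaining scope for variation then lies with those who left.

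**Number of interviews.** Two per group with 30 / 6 = 5 to 30 / 4 = 7.5 groups gives 10-15. The article therefore has three ranges: 10-15, 12-15 and 15-20. They need reconciling as a separate matter; the present point holds under each.

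**The case against.** The strongest reply is that a statement of timing is not an exclusion rule. In section 2.11 the end of the last session can be read as a date in the group's calendar, with no requirement that each interviewee was present. Participation rate is an explicit selection aim. The abstract and Table 2 place the interview in the week-12 post-test, section 2.11 allows 1-2 weeks for the post-tests, and the trial follows intention to treat. A participant who stopped sessions but came to the post-test could therefore be chosen. This stands: a reader might infer that early stoppers cannot be interviewed, and the documents do not say so. It does not supply a route, however. Selection after session 24 and an interview immediately afterwards still favour those who are there.

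A reader might also infer that the questions of motivation, retention and feasibility would be answered by completers alone. The documents do not support that. Section 7 raises motivation and retention as points of interest without assigning them to the interviews, and the topics in section 3.2.7 do not name them. The attendance records and discontinuation notes in section 2.15 cover people who leave. What these records are not said to contain is the leavers' own account of the experience.

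It is equally tempting to calculate how improbable a sample without early stoppers would be under random draws. That has no bearing here, because the sampling is purposive.

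Finally, the full protocol may hold recruitment detail that an article omits, and some people lost to the study will not be reachable by any rule. Both points are fair and lower the priority. The timing and selection rule is nevertheless stated in the article, and it pulls against the aims stated beside it.

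**Conclusion.** The concern holds in a limited form. As written, sections 2.11 and 3.2.7 make it unlikely, though not impossible, that intervention participants who stop early are interviewed. The exploratory data on experience would come mainly from those still attending and may be too favourable. If the 25% allowance carries over to stopping sessions in the intervention arm, the group concerned is about 7-8 of 30, equivalent to 3-4 of 12-15 or 4-5 of 15-20 interview places on a proportional basis. The direction of the bias is a reasonable expectation and cannot be shown from the documents. No primary or secondary quantitative comparison is affected. It is a cheap improvement of low priority.

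**What to change.** In sections 2.11 and 3.2.7, state that intervention participants who stop before session 24 are eligible for interview. Invite them when they stop, and interview them then or at the week-12 post-test. Keep some of the existing interview places for them, with unused places going to completers. When reporting themes, identify which come from completers and which from non-completers.

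The cost is a few sentences and earlier contact with those who stop. The number of interviews does not rise and the randomised comparison is unchanged. The drawbacks are that some will decline, that accounts given at week 12 may be less fresh, and that a few fewer completers are interviewed.
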